A telephone call-based self-monitoring and health coaching intervention would be responsive to the need for tech-agnostic self-monitoring for T2DM, but it is human resource-heavy. Hence, we are proposing artificial intelligence (AI)–assisted daily monitoring and automated health coaching as a scalable and low-cost alternative using the interactive voice response (IVR) system. The goal is to use accessible technology to optimize the reach and effectiveness of health coaching. To date, no study has reported using telephone calls for AI-assisted daily monitoring and health coaching focused on the four essential behaviors for glycemic control—PA, diet, medication adherence, and blood glucose monitoring. The daily nature of these automated calls for behavior monitoring presents a challenge for adherence. Rewards, especially monetary rewards, have been shown to provide significant extrinsic motivation toward behavior changes [31-33]. Gamification is also increasingly recognized as an effective method to stimulate adherence [34,35]. Very few studies have compared adaptive gamified financial incentives with fixed financial rewards. We incorporate gamification by implementing a gamified rewards scheme [31] based on participants’ consistency of answering daily self-monitoring calls to improve self-monitoring (tracking) behavior. GODART’s (Gamified Optimized Diabetes Management with Artificial Intelligence-Powered Rural Telehealth) theoretical framework is based on the social cognitive theory (SCT) for behavior change.

The proposed study aims to pilot GODART’s core feature: an automated behavior monitoring program using natural language processing (NLP) and two intervention components. The first intervention component (technology optimization experiment) will assess the feasibility of automated coaching and human coaching, and estimate preliminary effects of automated coaching compared to human coaching. The second intervention component (resource optimization experiment) will assess the feasibility of fixed and adaptive gamified rewards and estimate the preliminary effects of adaptive rewards compared to gamified rewards. Overall, we will assess the feasibility of our GODART study protocol in terms of recruitment, retention, and adherence. We hypothesize that the proposed interventions will be feasible and acceptable, and show early promise for reducing HbA_1c_ in adults with T2DM.

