### Randomization

Computer-generated randomization assignment was done for all consented participants. We implemented a permuted block randomization with varying block sizes, blinded to the assessment team. Participants were randomized to four experimental conditions based on a 2 by 2 factorial design with equal probability allocation. The randomization list is concealed within the REDCap randomization module. We have programmed this such that the participant can be randomized and allocated only to an experimental condition after it is confirmed that baseline data have been collected and entered. Once the primary outcome measures are entered in REDCap, the study staff members can assign the participants to their respective experimental conditions. The statistician and the Principal Investigators are blinded, but the participants and the health coach are not blinded. All participants enrolled in the study were randomized to one of the four arms:

Arm 1: Adaptive reward+weekly automated coachingArm 2: Adaptive reward+weekly human coachingArm 3: Fixed reward+weekly automated coachingArm 4: Fixed reward+weekly human coaching

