### Initial Personalized Orientation Session

All participants received an initial orientation session. Study team members served as health coaches, including a clinical registered dietitian and a certified health coach. During this session, the team reviewed the SKILLD survey completed as part of the baseline survey to identify gaps in the participants’ knowledge of T2DM management. These gaps were then addressed, and an introduction to the intervention was provided. The Diabetes Literacy and Numeracy Education Toolkit educational packet was used by health coaches during the orientation process to ensure all participants have equivalent baseline knowledge regardless of their literacy level. For participants with limited literacy skills, the health coaches used this call to walk participants through the educational materials, focusing on the visual components and providing detailed verbal explanations of all key information. This individualized approach ensured that participants who cannot read are still able to access, understand, and engage with the educational content, thereby establishing a consistent foundation of T2DM management knowledge across the study population.

This call provided key information about the intervention, including expectations for the telephone-based ABMS and health coaching calls, participants’ randomization to fixed or adaptive rewards, and recommended use of a glucometer and pedometer. Participants also listened to a sample ABMS call to learn best practices for voice recognition when reporting step counts, medication use, and blood glucose testing.

The call included instructions to improve the completeness and accuracy of diet records, with reminders about commonly forgotten items (eg, beverages, condiments, and sweeteners) and guidance to avoid brand names for better matching in Nutritionix. Participants also received introductory nutrition education focused on making healthy replacements to support glycemic control, specifically limiting added sugars, refined carbohydrates, and saturated fats. These behaviors are tracked through daily ABMS calls and discussed during weekly health coaching sessions to enhance both the accuracy and efficiency of self-monitoring.

Following the orientation call, all participants were activated in the ABMS and began receiving calls starting the following Monday.

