#### Experimentation Group 2: Adapted Versus Fixed Gamified Reward Levels

Participants in this group are randomized into two arms: fixed-reward levels and adapted gamified reward levels; the total possible amount earned over the period of 24 weeks in each arm is US $100.80. The purpose of the rewards is to conduct daily self-monitoring, not as incentives per se to participate in the study. In the fixed-reward arm, participants receive 60 cents per day for answering daily monitoring calls for 24 weeks, earning up to US $100.80 if they answer daily. In the adapted gamified reward arm, participants’ daily rewards increase weekly, starting at US $0.20 per day in the first week, US $0.25 per day in the second, US $0.30 per day in the third, and US $0.65 per day from the fourth week until the end of the study at 6 months. In this arm, missing one day of monitoring (in the past 7 days) drops the reward value by one level (eg, from US $0.65 to US $0.30), with additional missed days dropping the reward further. Participants can rebuild their reward levels by consistently answering daily calls. Like the fixed award arm, a participant answering the call daily for 24 weeks receives up to US $100.80. This resource management–driven study arm will inform us of the extent to which rewards can enable successful behavior change.

### Postintervention Assessments at Month 6

At month 6, similar to the baseline visit, each participant is asked to visit their nearest LabCorp location to provide a blood sample for HbA_1c_, lipid profile, and biometrics. Participants are also sent a 6-month survey packet either electronically via email using REDCap or via physical mail, depending on the participant’s preference. This packet includes all of the surveys in the baseline packet in addition to: Speech User Interface Service Quality, which evaluates the quality, perceived ease of use, and user satisfaction of speech-based interfaces [54]; System Usability Scale, which measures system usability [55]; and the theoretical framework of acceptability survey [56] which assesses the acceptability of the intervention.

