### Outcomes

We are collecting feasibility, process, clinical, and patient-reported outcomes (PROs) during the intervention, with feasibility outcomes serving as the primary end points. As outlined in Tables 2 and 3, our primary outcomes include key feasibility indicators: recruitment, retention, and adherence to the intervention. Secondary outcomes include other feasibility measures such as process measures (eg, time to recruit, percentage of missing data, and enrollment rate), and selected patient-centered and clinical outcomes. The choice of clinical and patient-reported assessments is based on guidelines from the American Diabetes Association [57]. Specifically, diabetes distress is a key PRO, while HbA_1c_ and weight are the key secondary clinical outcomes. Exploratory outcomes include additional PROs (eg, quality of life, depression, self-efficacy, and acceptability of the intervention) and clinical indicators such as blood pressure and lipid profile. PROs are collected using validated instruments such as the Diabetes Distress Scale, EQ-5D, Patient Health Questionnaire-4, and the Diabetes Empowerment Scale. Intervention acceptability is assessed using the Speech User Interface Service Quality, System Usability Scale, and theoretical framework of acceptability scales, in addition to qualitative exit interviews. PA is measured using step count data. Adherence data, including daily self-monitoring of blood glucose and medication adherence, are collected through the ABMS IVR system.

In addition to recruitment, retention, and adherence-related measures, other feasibility measures include process, resource, and management measures such as attrition rate, coach time, time to recruit participants, and technology delivery-related issues (Table 3).

**Table 2 table2:** GODART^a^ outcome measures.

			Instrument	Mode of collection	Collection timepoint	Outcome type

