#### Analytic Strategy for Preliminary Effectiveness Analyses

We will also estimate effect sizes as preliminary effectiveness estimates. All statistical analyses will follow an intent-to-treat approach. In line with a pilot study, we will also report 75% and 85% CI estimates in addition to the traditional 95% CIs to further aid in the statistical interpretation of the findings [65]. We will use linear mixed models to estimate effects by accounting for correlated data and benefit from the maximum likelihood estimation procedure that uses all information in the dataset in the presence of missing outcome data. Our overall approach will be similar to Pellegrini et al [38]. To evaluate the main effect of each component on pre-post differences in outcomes, we will use baseline as the reference cell to determine differences in change across time (ie, 6 months vs baseline) [38]. However, these effects will be statistically modeled as component-by-time interactions, with the 6-month outcome as the primary end point. We will also include two-way interactions between components (eg, Factor 1 by Factor 2 by time interaction). We will then identify all the active components or combinations of components, where active is operationalized as a mean reduction of 0.5 units (%) in HbA_1c_ between baseline and month 6 [66,67]. Similar analyses will be done for secondary outcomes. Where information related to minimally clinically important differences is available, we will use it to assess whether the combination is active. For example, an average 5% weight loss is considered to be active in the case of weight. We will leverage the generalized linear modeling framework and resampling-based approaches for nonnormal outcomes. We will conduct exploratory analyses to assess biases in the self-reported PROs. While we are not statistically powered to do mediation or moderation analyses, in line with the MOST Preparatory Phase, we will conduct exploratory mediation and moderator analyses using our tracking data as potential mediators or moderators.

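### Tracking data collected after randomization, which the reward factor is meant to change, should not be used as moderators of component effects, even in an exploratory analysis

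*Protocol article*

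**What the plan says.** The analysis is announced in the Protocol article, Analytic Strategy for Preliminary Effectiveness Analyses: "we will conduct exploratory mediation and moderator analyses using our tracking data as potential mediators or moderators". The same section calls this work exploratory and says that the study is not powered for it. It sets no limit on which variables may act as moderators.

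Other sections fix when these data arise and what acts on them:

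- Outcomes: "Adherence data, including daily self-monitoring of blood glucose and medication adherence, are collected through the ABMS IVR system".
- Randomization: a participant "can be randomized and allocated only to an experimental condition after it is confirmed that baseline data have been collected and entered".
- Initial Personalized Orientation Session: participants hear about their reward assignment in this session, and then "Following the orientation call, all participants were activated in the ABMS and began receiving calls starting the following Monday".
- Introduction: the reward scheme rests on "participants’ consistency of answering daily self-monitoring calls to improve self-monitoring (tracking) behavior".
- Experimentation Group 2: "The purpose of the rewards is to conduct daily self-monitoring, not as incentives per se to participate in the study". In the adaptive arm, "missing one day of monitoring (in the past 7 days) drops the reward value by one level".

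**The concern.** A moderator analysis asks whether a component works differently in different kinds of participant, so the variable that defines the kinds must be fixed before assignment. Here every call-based tracking value follows assignment, and one of the two factors is built to move it.

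Suppose the adaptive reward raises call answering. At the same answering rate, participants on the adaptive reward are then on average less motivated than those on the fixed reward, because they needed a stronger inducement to get there. If motivation also influences HbA1c, the two groups differ at month 6 even when the reward has no effect on HbA1c. In this case the adaptive reward would look harmful at equal engagement. This happens even if every day of tracking is observed, so it is not a missing-data problem.

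The pilot is meant to inform a later optimization trial, and the Strengths and Limitations section expects analyses of the call data to support just-in-time adaptive interventions. A spurious statement about engaged participants could be carried forward into either. The power caveat warns of imprecision. It does not warn of bias, which a larger sample would only make more likely to reach significance.

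**Working it through.** **1. Timing and mechanism.** Baseline entry comes first, then randomization, then orientation with disclosure of the reward, then the first monitoring call the following Monday. No run-in is described, so no call-based tracking value precedes assignment. Rewards are paid for answering these calls, so tracking can be a consequence of the reward factor.

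**2. The plan's own figure.** The article gives none for the moderator analysis. The nearest is the main-effect power in Sample Size Justification: 88 participants, 15% attrition, pre-post correlation 0.5, type 1 error 0.05 (two-sided assumed), d = 0.572.

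- Analysed: 88 × 0.85 = 74.8, taken as 74, or 37 per level.
- Standardized effect: 0.572 / [√(1 − 0.5²) × √(2/37)] = 0.572 / (0.8660 × 0.2325) = 2.84.
- Normal approximation: Φ(2.84 − 1.96) = 0.811. The noncentral t gives 0.800.
- In HbA1c units: 0.572 × 1.5 = 0.858.

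The stated 80% and 0.86% reproduce and are not in dispute. They supply the sample size, SD and correlation used below.

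**3. Simulation with no true effect on HbA1c.** From the article: 74 analysed, SD 1.5%, pre-post correlation 0.5, and 24 × 7 = 168 calls. Assumed, because the article gives no figures: the shift a in call answering, the slope g of engagement on motivation, and the residual correlation r between motivation and HbA1c.

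- Engagement: binomial(168), with logit = 1.5 + a·R + g·U + N(0, 0.8). R is the reward level, U is unmeasured motivation, and g = 0.8.
- Month-6 HbA1c in SD units: 0.5·baseline + √0.75·[−r·U + √(1 − r²)·e]. There is no R term.
- Fitted model: HbA1c on baseline, R, centred engagement and R × engagement, with 4,000 trials per setting and two-sided 5% tests.

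At average motivation, a = 1.0 moves answering from about 82% (logit 1.5) to about 92% (logit 2.5).

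False-positive rates (%) at r = 0.3 / 0.5 / 0.6:

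| Setting | Component term at average engagement | Interaction |
|---|---|---|
| a = 0 | about 5 | about 5 |
| a = 0.5 | 6.4 / 9.6 / 11.0 | 4.9 / 5.9 / 6.1 |
| a = 1.0 | 9.6 / 19.7 / 28.3 | 5.8 / 8.7 / 10.5 |
| a = 1.0, g from 0.2 (fixed) to 1.2 (adaptive) | not the point of this row | 8.3 / 15.1 / 20.3 |

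At a = 1.0 the spurious HbA1c difference at average engagement is 0.22, 0.36 and 0.44 percentage points. The randomized contrast without engagement in the model rejects in 4% to 6% of trials throughout.

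**4. A second model with other assumed values.** A shift of 0.8 log-odds gives 11–14% (r = 0.3) and 26–31% (r = 0.5) for the component term, and 5–7% for the interaction. In an extreme case where the reward removes the link between motivation and tracking entirely, the interaction rate is 9–19% with continuous tracking and 15–38% if tracking is split at 80% of calls. With a moderator fixed before randomization, both terms return to about 5%.

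**5. Does the mediator role escape this?** No. Under the model of step 3 with a = 1.0 and g = 0.8, engagement has no effect on HbA1c, so the direct and indirect effects are both truly zero. At r = 0.3 / 0.5 / 0.6 the direct effect is falsely significant in 10 / 16 / 24% of trials. The joint-significance test of the indirect effect is falsely significant in 33 / 72 / 84%.

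**The case against.** The case on the other side has several strong parts.

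- **The moderation test proper is the interaction, and it is only modestly inflated.** This stands. Under a common shift of up to 1.0 log-odds it stays at about 5% to 11%. Higher rates need the reward to change who engages, for which the article gives no evidence. Most of the distortion falls on the component effect read off at a given tracking level.
- **The engagement shift may be small.** This stands too. Both reward arms have the same maximum of US $100.80, and nothing in the text implies a shift of 1.0 log-odds. That is why the range includes zero shift, where no inflation appears.
- **Only the reward factor was simulated.** True. Coaching gives weekly feedback on the tracked behaviours, so the same argument may apply to it, but no size is claimed.
- **The article specifies no moderator model, and the analysis plan may do so.** The model above is indeed an assumption. The source of the moderators, however, is a choice the article states, not a detail it leaves out.
- **Listing one variable as mediator or moderator is not a contradiction.** Agreed. Mediation models may include a component-by-mediator interaction. The point is the loss of randomization's protection, not inconsistent wording.

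A reader might infer that this analysis would steer which components go forward. The documents do not support that. An active component is defined by a 0.5% mean HbA1c reduction in component-by-time models under intent-to-treat, and no tracking term enters that rule.

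**Conclusion.** The point holds as a minor-to-moderate correction to an exploratory analysis. Tracking data arise after randomization and are a target of the reward factor, so a component effect at a given tracking level is not a randomized comparison. With no true effect on HbA1c, residual correlation 0.3 to 0.6 and a shift of 0.5 to 1.0 log-odds, the false-positive rate is about 6% to 28% for the component term. For the interaction it is about 5% to 11%, or up to about 20% with continuous tracking if the reward also changes who engages.

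These sizes depend on assumed confounding and an assumed engagement shift. The direction of the problem follows from the document; its magnitude does not. It would be wrong to infer that the analysis must give false results, or that the trial's main conclusions are compromised: the feasibility endpoints, the intent-to-treat main effects and the 0.5% rule are untouched. It would also be wrong to infer that using tracking data only as mediators removes the bias, since the same confounding affects direct and indirect effects.

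**What to change.** Amend the sentence on mediation and moderation in three ways.

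1. Limit moderators to variables recorded before randomization and already collected: for example baseline HbA1c, age, gender, race, urban or nonurban status, insurance, SKILLD and the Diabetes Distress Scale.
2. Report component results by level of engagement only as descriptive associations, not as moderation of a component effect.
3. If tracking data remain as mediators, state that the direct and indirect effects assume no unmeasured mediator-outcome confounding, adjust for baseline covariates, and add a sensitivity analysis for that confounding.

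No new data are needed. The cost is a few sentences and a little more analysis work, and engagement-by-component results can no longer be presented as effect moderation.

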#### Analysis of Qualitative Interviews

Collected interview data will be analyzed using a phenomenological approach. Two researchers will independently code the transcribed audio-recorded interviews. They will meet after coding every four transcripts to discuss and resolve any discrepancies in coding. A third researcher will be available to adjudicate unresolved discrepancies. Coding will follow an inductive, emergent approach grounded in the transcript data, using both descriptive and in vivo codes. The coding process will involve two levels: first-cycle coding, where initial codes are assigned using in vivo coding, and second-cycle coding, where these codes are refined and grouped into broader themes using pattern coding [68]. The codebook structure will include themes, codes, and text examples of quotes. Thematic saturation will guide the final sample size. We will enhance trustworthiness through triangulation, peer debriefing, and maintaining an audit trail. All qualitative analyses will be done using NVivo 12 Plus (Lumivero).

## Results

We conducted 1938 phone contact attempts, resulting in 1192 participants completing phone screening. Of those, 162 were deemed potentially eligible and consented to screen for HbA_1c_. As of October 2025, 88 participants who were randomized and enrolled in the study have completed the 6-month follow-up. We anticipate completing data analysis by December 2025. Table 4 outlines the study timeline and anticipated completion of key milestones.

**Table 4 table4:** Timeline of study progress and anticipated target completion.

	2022					2023					2024					2025			
	Q1	Q2	Q3	Q4	Q1		Q2	Q3	Q4	Q1		Q2	Q3	Q4	Q1		Q2	Q3	Q4
Institutional Review Board approval				✓	✓														
Manual of Operating Procedures development and refinement	✓	✓	✓	✓	✓		✓	✓											
Recruitment period									✓	✓		✓	✓	✓					
Intervention period									✓	✓		✓	✓	✓	✓		✓		
Baseline assessment									✓	✓		✓	✓	✓					
6-month assessments									✓	✓		✓	✓	✓	✓		✓		
Data management and quality control									✓	✓		✓	✓	✓	✓		✓	✓	✓
Exit interview									✓	✓		✓	✓	✓	✓		✓		
Data analysis															✓		✓	✓	✓
Publications																	✓		✓

